### **Definitions to guide causal relationship SAE:**

- |                      |                                                                                                                                                            |
|----------------------|------------------------------------------------------------------------------------------------------------------------------------------------------------|
| Very Likely/Certain: | A clinical event with a plausible time relationship to intervention and which cannot be explained by concurrent disease or other drugs or chemicals.       |
| Probable:            | A clinical event with a reasonable time relationship to intervention; is unlikely to be attributed to concurrent disease or other drugs or chemicals.      |
| Possible:            | A clinical event with a reasonable time relationship to intervention, but which could also be explained by concurrent disease or other drugs or chemicals. |

|                 |                                                                                                                                                                                         |
|-----------------|-----------------------------------------------------------------------------------------------------------------------------------------------------------------------------------------|
| Unlikely:       | A clinical event whose time relationship to intervention makes a causal connection improbable, but which could be plausibly explained by underlying disease or other drugs or chemicals |
| Unrelated:      | A clinical event with an incompatible time relationship and which could be explained by underlying disease or other drugs or chemicals.                                                 |
| Unclassifiable: | A clinical event with insufficient information to permit assessment and identification of the cause.                                                                                    |

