## Description of the Research Project

**Hypothesis to be tested:** We hypothesize that Diarrheal Etiology Prediction (DEP) algorithm for calculating probability of viral etiology of diarrhea will safely reduce inappropriate antibiotic use among children <5 years old with acute diarrhea.

**Primary objective:** To examine the acceptability and impact of a Diarrheal Etiology Prediction (DEP) among physicians treating children with diarrhea.

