### Background of the Project including Preliminary Observations:

Diarrhoeal diseases are a leading cause of morbidity and mortality in children worldwide, with an estimated one billion cases and 500,000 deaths annually. While the majority of deaths due to diarrhoea occur in lower-income countries, infectious diarrhoea remains a significant problem in high-income countries. Aside from the immediate morbidity, potential long-term sequelae of diarrhoea in children in low-resource settings include malnutrition, growth faltering, and deficits in cognitive development.

While the cornerstone of diarrhoeal disease management in children is rehydration, a number of other management decisions, including the use of antibiotics and laboratory testing, may impact the course of disease. Overuse of antibiotics may cause side-effects and lead to increased antimicrobial resistance in the community. Underuse of antimicrobials for some bacterial and protozoal pathogens may lead to prolonged duration of illness and facilitate transmission. This can result in increased days of school or parental work missed, and among malnourished children in resource-poor settings, potential for growth faltering or death. Overuse of laboratory testing may have financial impact on both the patient and the healthcare system, and underuse may delay appropriate therapy or prevent recognition of outbreaks. Thus, accurate and cost-effective determination of diarrhoea etiology is important for proper case management in children and for public health.

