## Research Design and Methods

**Strategic Plan Overview:** This is a randomized crossover study, where clinicians will be randomized to periods where they will use a rehydration calculator application with or without the DEP. The crossover will include a washout period to reduce carryover effect. The study will be conducted over a 9-week period. We will use a random number generator to randomize clinicians to DEP or control arm for the first 4 weeks. After the first 4 weeks, there will be a 1-week washout period without decision support, after which each clinician will cross-over to the other arm for the next 4 weeks.

The DEP algorithm involves entry of clinical variables (age, bloody diarrhea, Breastfeeding, vomiting, mid-upper arm circumference- MUAC). The output provides the probability that the cause of the diarrhea is viral.

The DEP will be integrated as a feature into a Rehydration Calculator application that has previously been tested as part of two clinical studies in Bangladesh (icddr,b/ IEDCR; Khan AI et al, submitted 2019 and Haque et al. PLoS NTD 2017). The Rehydration Calculator with the DEP turned 'off' will serve as a control. The experimental arm of the study will have the DEP turned 'on'. The Rehydration Calculator is an electronic decision-support tool that provides recommendations for rehydration based on entry of age, gender, weight, and dehydration status. Given the outcome measures of this study, the Rehydration Calculator will be configured to not give antibiotic recommendations.

**Study Sites:** 4 Healthcare Facilities in Mali. ( CSRef CV, ASACOSAB1, CSRef CVI, ASACOYIR)

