### c.ii. Study population and enrolment:

We will enrol both 1) diarrhea-treating clinicians, and 2) children presenting with acute diarrhea.

We will use the following inclusion/exclusion criteria for enrolling clinicians:

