### **Assessment of Safety**

All adverse events which are observed actively or reported/volunteered by subject/guardian will be recorded with information about severity (i.e., whether mild, moderate or severe) and possible relation to the study intervention by the study physician. In case of any serious adverse events, the investigator will notify DSMB immediately by telephone/facsimile/email within 24 hrs and take appropriate measures to safeguard the participants. Every SAE must be reported, even if the Investigator considers that it is not related to the intervention. The Completed serious adverse event (SAE) form should be submitted to DSMB within 72 hours either by fax, or by email.

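### The SAE causality scale is written for drug toxicity, so harm from a wrong viral prediction and a withheld antibiotic would ordinarily be graded no higher than Possible, the same as incidental worsening

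*Protocol*

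**What the plan says.** The protocol's section Assessment of Safety has each adverse event recorded with its "possible relation to the study intervention by the study physician". The table under Definitions to guide causal relationship SAE is the only guide supplied for that judgement. Three of its grades turn on concurrent disease:

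- *Very Likely/Certain* is the label for this: "A clinical event with a plausible time relationship to intervention and which cannot be explained by concurrent disease or other drugs or chemicals".
- For *Probable*, the timing must be reasonable, and the event "is unlikely to be attributed to concurrent disease or other drugs or chemicals".
- For *Possible*, the timing must be reasonable, "but which could also be explained by concurrent disease or other drugs or chemicals".

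*Unlikely* and *Unrelated* depend on timing that makes a causal link improbable or incompatible. *Unclassifiable* is for insufficient information.

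On the intervention, Research Design and Methods says: "The output provides the probability that the cause of the diarrhea is viral". The hypothesis in Description of the Research Project is that the algorithm "will safely reduce inappropriate antibiotic use among children <5 years old with acute diarrhea". The Background section names the route of harm: "Underuse of antimicrobials for some bacterial and protozoal pathogens may lead to prolonged duration of illness and facilitate transmission". It goes on to mention possible growth faltering or death in malnourished children.

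**The concern.** These definitions suit a product with direct toxicity, where the patient's disease is a rival explanation for a bad event. The DEP has no such toxicity. It can harm a child if a bacterial illness is shown as probably viral, the clinician orders no antibiotic, and the illness progresses. Here the disease is the pathway of harm, yet the scale treats it as a reason to mark the grade down.

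The hypothesis includes safety, so the reading of related events matters. If the final report said that no SAE was probably or certainly related to the DEP, readers could take that as reassurance when the grading rule had made it nearly inevitable. Elsewhere the protocol does not fill the gap. The section on ethical assurance names only technical error as a risk of the DEP. A rule that works as designed, with a cross-validated AUC of about 0.85, will still misclassify some children.

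**Working it through.** No arithmetic applies: the point depends on no rate, effect size or sample size. The check applies each grade to two cases.

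**Inputs**

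1. Every patient enrolled has the index disease: the study recruits "children presenting with acute diarrhea" (Study population and enrolment).
2. The DEP acts only by showing a viral probability to the clinician (Research Design and Methods).
3. Under-treatment of bacterial or protozoal illness is a recognised harm (Background). Only children below a MUAC cut-off for severe malnutrition are excluded, so less malnourished children can enrol.
4. An SAE is death, significant disability or a life-threatening situation, up to 10 days after discharge (Definitions of Serious Adverse Events).

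**Case A.** The DEP shows a high viral probability, no antibiotic is ordered, and a bacterial diarrhoea becomes life-threatening within days.

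**Case B.** The same worsening with the same timing, but the DEP output played no part in the treatment decision.

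| Grade | Case A | Case B |
|---|---|---|
| Very Likely/Certain | Fails: the child's diarrhoeal disease explains the event | Fails, same reason |
| Probable | Fails: the event is readily attributed to that disease | Fails, same reason |
| Possible | Met: timing reasonable, disease could also explain it | Met |
| Unlikely | Not met: timing is not improbable | Not met |
| Unrelated | Not met: timing is not incompatible | Not met |

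Both cases come out as *Possible*. The scale gives the harm that the Background section describes and background disease the same label.

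**How far this depends on the wording.** The tests for the two top grades differ. *Very Likely/Certain* requires that disease cannot explain the event. *Probable* asks only that disease be an unlikely explanation, a softer judgement, but worsening of the presenting diarrhoea fails it too. The result also requires that concurrent disease include the presenting diarrhoea. That is the ordinary reading. However, the table speaks of concurrent disease in its upper grades and underlying disease in its lower ones, and defines neither. A rater who took concurrent disease to mean only some other illness would not face the ceiling. Two raters could then grade the same event differently, which is also a fault in the definitions.

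**The case against.** The strongest reply is that nothing in the protocol hangs on the grade. Assessment of Safety sends every SAE to the DSMB within 24 hours even when the investigator judges it unrelated. No reporting, stopping, endpoint or analysis rule refers to the grade, and a separate monitoring plan is still to be written. All of this stands, and it limits the consequence to labelling and interpretation.

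A reader might infer that the DSMB would have no signal of related events, or that the report would show none. The documents do not support that. *Possible* is an affirmative grade, above *Unlikely* and *Unrelated*, and nothing says it will be counted as unrelated or left out. A reader might also infer that the DEP's harm could never, under any reading, be graded above *Possible*. That goes too far, because it depends on an undefined term.

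Safety also does not rest on single-case attribution alone. Symptom resolution at 10 days is a secondary outcome, and persistence of symptoms, returns to healthcare and medication use are collected by telephone in both arms. A comparison of randomised arms needs no causality grade. This stands as well.

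It can be said that *Possible* is fair for one child, since nobody can know whether that child would have worsened anyway. That is partly right, but it does not justify a rule that closes the higher grades before the rater has considered what the app showed and what was ordered.

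Finally, few such events are likely. On the planning figures, each arm has 15 × 12 = 180 children, and a fall from 90% to 80% leaves 0.10 × 180 = 18 more children without antibiotics. If 1% to 5% of these had an SAE (an assumption; the protocol gives no rate), that is 18 × 0.01 = 0.18 to 18 × 0.05 = 0.9 events. So the grading would affect very few events, but with numbers this small the label on each one carries much of the narrative.

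A reader might suppose that the person grading is one of the randomised clinicians. The protocol says only study physician, so that is not established.

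**Conclusion.** The concern holds in a limited form. If concurrent disease covers the presenting diarrhoea, an SAE following a wrong viral prediction and a withheld antibiotic is graded no higher than *Possible*, the same as an incidental worsening with reasonable timing. The scale cannot separate the two. A finding of no probably or certainly related SAEs would therefore say little about whether the DEP reduced antibiotic use safely.

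The size is qualitative: a ceiling on the grade for one route of harm, which is the one the protocol itself names. SAE reports are not lost, and the primary analysis is untouched. The conclusion assumes the ordinary meaning of an undefined term and that raters apply the table as written.

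**What to change.** Amend the causality table in two respects.

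1. State that worsening or complication of the presenting infection does not by itself count as an alternative explanation that rules out *Probable* or *Very Likely/Certain*.
2. State that the rater considers whether the study app's output, with the DEP on or off, may have contributed to the treatment decision that preceded the event.

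This grading is asymmetric by arm, because children in control periods have no DEP output to which an event could be related. The count of related events should therefore not carry the safety comparison. Base that comparison on all SAEs tabulated by arm and period regardless of attribution, and list for each event the probability displayed (where there was one) and whether an antibiotic was ordered. If the statistical analysis plan or the monitoring plan already specifies such a table, only the change to the definitions is needed.

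The cost is a short amendment and slightly more reporting work. More events will be graded as related in the DEP arm, which is why the unattributed table should be primary. No clinical rule, sample size or primary analysis changes.

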## **Ethical Assurance for Protection of Human rights**

Justification of conducting research in human participants that are sick: The questions asked herein can only be studied in humans because we are interested in how best to develop a DEP algorithm for humans to improve clinical care.

Benefits: Patients will likely have no immediate benefit. All populations at risk from diarrhoeal disease will benefit by the knowledge gained and development of an DEP.

Risks: We are comparing the effect of a DEP on antibiotic orders in the context of WHO guidelines. These guidelines and calculations have been extensively reviewed and tested in previous studies at CVD-Mali. Despite these efforts, patients will remain at minor risk that technical errors may occur in the DEP. To minimize this risk, the DEP has been tested in a pilot study in Mali.

### Protections of participant human rights.

*Clinical.* Standard of care for the treatment of patients with diarrhoeal disease will be maintained throughout this study. There will be no differential treatment to specific genders, age groups, races, and cultures. There are also no special procedures or invasive procedures included in this study. Patient histories taken during patient care directly related to the demographic and clinical information are required to treat the patient and identify public health interventions that will benefit the community (e.g. diarrhoeal disease cluster analysis).

*Confidentiality.* One risk is a breach in confidentiality (see privacy protection sections). In brief, to address this risk, data collected via the application will be stored on a secure, password protected computer interface. No data will be stored permanently on mobile devices. Data will be transiently stored on the devices when there is no mobile connectivity. All devices will be password protected and encryption occurs at each point in the software architecture. Access to the server will be restricted, and when possible, data will be coded before analysis. Data analysis performed in the United States will be stored on a local secure, HIPAA compliant server. All paper documents will be stored in a locked container with limited access governed by the study PI.

### Individual privacy.

*Privacy protections:* Diarrhoeal disease patients need to be assessed rapidly in hospital triage setting. Although there is limited time and space to assure complete privacy, staff maintain appropriate protocols for the protection of privacy during the triage and admission process.

*PHI confidentiality:* Health information will include: demographic data (e.g. name, birth date, residence location, hospital location, telephone number), clinical data (e.g. number of stools, watery, bloody, vomiting, medications taken for the illness, allergies), and biometric data (weight and MUAC). PHI institutional regulations will be followed. When there is a need for US-based staff to work with PHI or import PHI into the United States, staff will comply by US NIH HIPAA based regulations.

*Access to the data:* Access to the data is based on levels of access: (i) Collection of clinical information by the research staff and (ii) Access to the database (PHI): core-research team and named key personnel in the (USA).

*Education of staff:* We will assure that all staff takes personal health information privacy training.

*Safe-guards:* Physical: As mentioned, standard of care will be performed during this study. Oversight will come immediately by the Senior Field Assistant (Trained Field Assistant) who will report to the Study Doctor.

*Financial:* There is no cost to participate in the study.

*Social concerns:* Unanticipated social concerns will be evaluated in partnership and alignment meetings across all collaborators and local hospital staff/leaders.

*Conflict of interest:* The study investigators and affiliates hold NO patents or stock in the decision-support technologies.

### **Collaborative Arrangements**

*Data sharing.* The data ownership, access and security of personal health information related to this study will abide by CVD-Mali policies. These policies will be honoured by University of Utah, University of Maryland, and CVD-Mali investigators. For these reasons, primary access to the data will be governed by [name] (CVD-Mali PI).

*Intellectual Property.* The study investigators and affiliates hold NO patents or stock in the decision-support technologies. The algorithms used in the software are derived from publicly available WHO protocols. Therefore, there is no intellectual property to be secured in regards to the decision support because these are published protocols.

*Authorship.* Authorship will be granted based on CVD-Mali, University of Utah and University of Maryland policies. In general, all members of the team that contribute essential materials, significant contributions to experimental design, implementation, and data analysis, and participate in the writing manuscripts will be offered authorship.

*Sample collection.* Not applicable.

